#### Secondary analyses

We will perform similar analysis on TNF-α, IL-6 and MCP-1 (as well as other important inflammatory molecules). We will use Pearson's correlation techniques (as well as adjusted linear regression) to determine whether changes in CRP levels correlate with changes in SGRQ scores. Previous studies indicate that SGRQ improves with fluticasone with or without salmeterol, independent of their effects on FEV_1 _[10]. We hypothesize that SGRQ may correlate with CRP.

#### Sample size calculation

We will enroll 250 participants with COPD for this study. This will permit 100 participants to be assigned to fluticasone and combination treatment groups, respectively, and 50 participants will be exposed to a placebo during the active treatment phase. We have calculated our sample size based on the following assumptions: 1) we anticipate that fluticasone relative to placebo will lower baseline CRP levels by ~1.5 mg/L with standard deviation of 3.5 mg/L; 2) we will perform between group comparison of CRP (from baseline) using independent two sample t-test at alpha of 0.05 (two-tailed) and a power of ≥80%.

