**Methods/Design:**

After a 4-week run-in phase during which patients with stable chronic obstructive pulmonary disease will receive inhaled fluticasone (500 micrograms twice daily), followed by a 4-week withdrawal phase during which all inhaled corticosteroids and long acting β_2_-adrenoceptor agonists will be discontinued, patients will be randomized to receive fluticasone (500 micrograms twice daily), fluticasone/salmeterol combination (500/50 micrograms twice daily), or placebo for four weeks. The study will recruit 250 patients across 11 centers in western Canada. Patients must be 40 years of age or older with at least 10 pack-year smoking history and have chronic obstructive pulmonary disease defined as forced expiratory volume in one second to vital capacity ratio of 0.70 or less and forced expiratory volume in one second that is 80% of predicted or less. Patients will be excluded if they have any known chronic systemic infections, inflammatory conditions, history of previous solid organ transplantation, myocardial infarction, or cerebrovascular accident within the past 3 months prior to study enrolment. The primary end-point is serum C-reactive protein level. Secondary end-points include circulating inflammatory cytokines such as interleukin-6 and interleukin-8 as well as health-related quality of life and lung function.

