## Methods/design

### Overview of the study design

This trial is a double blind study comparing the effects of inhaled fluticasone alone or in combination with salmeterol against placebo on serum CRP levels in COPD. All study participants will first undergo a run-in phase during which they will be treated with fluticasone 500 mcg bid for 4 weeks. This will be followed by a withdrawal phase wherein all participants will be free of any inhaled corticosteroids or theophylline products for 4 weeks. After the withdrawal phase, participants will be randomly assigned to one of three arms: placebo; inhaled fluticasone (500 mcg bid); or inhaled fluticasone/salmeterol combination (500/50 mcg bid). Randomization will be carried out centrally according to a computer-generated sequence stratified according to current smoking status with allocation concealment in a 1 (placebo arm) to 2 (fluticasone arm) to 2 (combination arm) distribution ratio. In this phase, all participants and study personnel will be blinded to the treatment assignment. This phase will last for 4 weeks. For safety reasons, during severe exacerbations (i.e. those requiring hospitalization or emergency visit for COPD), the treating physician can break the "code" and place study participants on medications needed to treat the exacerbation (See Figure 1 for protocol summary)

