## Discussion

In this paper, we have reported the background, the rationale, and the study protocol for a unique multi-center randomized controlled trial whose main outcome is a biochemical measurement (i.e. CRP). The study will test the hypothesis that inhaled corticosteroids alone or in combination with a long-acting β_2_-adrenoceptor agonist will reduce CRP levels in stable COPD patients. To our knowledge, this is the first clinical trial in COPD whose main outcome is serum CRP. Additionally, this study will be able to determine the effects of these medications on other relevant inflammatory biomarkers and likely provide a solid biological rationale for the clinical effects of inhaled corticosteroids and combination therapy in COPD.

There are certain limitations of this trial. Firstly, the study will not measure any parameters of inflammation in the lung. We decided against collecting biological samples from the airways because: 1) a recently conducted and published randomized controlled trial demonstrated that combination therapy reduces airway inflammation [20,21]; 2) there remains considerable amount of controversy regarding the utility of exhaled condensates and induced sputum in assessing airway inflammation in COPD [28]; 3) more invasive measurements (e.g. bronchoscopy) would have significantly reduced the projected recruitment rate of participants, reducing the power of the study to detect relevant differences in CRP; and 4) the primary focus of this study was to assess the effects of combination and steroid therapy on systemic inflammation. Secondly, the study has a relatively short follow-up period. We decided against a longer period of follow-up for pragmatic reasons. In our previous pilot study, we observed significant changes in CRP with inhaled corticosteroids after only 2 weeks of treatment [15]. Additionally, we were concerned that follow-up longer than four weeks would be associated with increased drop-out rates, and exacerbations, reduced compliance with the study medications, and changes in medications (both pulmonary and nonpulmonary drugs) that may alter CRP levels. Thirdly, we cannot be certain that changes in CRP levels will necessarily result in significant changes in health outcomes of COPD patients, though there is a body of indirect evidence suggesting that they do [6,14,17]. Additional work is needed in future studies to establish a causal link between CRP and health outcomes in COPD.

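### The 250 is counted at enrolment, before 8 weeks of run-in and withdrawal, yet is equated with 100/100/50 assigned, so the stated arms and power allow for no loss

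*Protocol article*

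**What the plan says.** The Sample size calculation section opens with "We will enroll 250 participants with COPD for this study" and continues: "This will permit 100 participants to be assigned to fluticasone and combination treatment groups, respectively, and 50 participants will be exposed to a placebo". The abstract gives the same total: "The study will recruit 250 patients across 11 centers in western Canada". The arm sizes match the allocation in the Overview of the study design, "in a 1 (placebo arm) to 2 (fluticasone arm) to 2 (combination arm) distribution ratio".

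The same overview sets the order of events. "All study participants will first undergo a run-in phase" of 4 weeks on fluticasone. A 4-week withdrawal phase follows, then randomisation, then 4 weeks of blinded treatment. The section on exacerbations gives patients their instructions at enrolment for the whole study period, and the eligibility criteria date exclusions back from enrolment. In both places enrolment means study entry. The section on the active treatment phase says that all participants will be randomised.

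The planning assumptions are that fluticasone relative to placebo will "lower baseline CRP levels by ~1.5 mg/L with standard deviation of 3.5 mg/L", tested by an "independent two sample t-test at alpha of 0.05 (two-tailed) and a power of ≥80" per cent. None of the listed assumptions concerns loss.

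**The concern.** The article prints an equality between a number counted at entry and a number counted 8 weeks later. In those 8 weeks patients change their usual inhaled treatment, then go 4 weeks without inhaled corticosteroids or long-acting β2-agonists, and are told to report any worsening. Anyone who leaves in this period belongs to no arm, and an intention-to-treat analysis cannot bring them back. Anyone who is randomised but has no week-4 CRP contributes no change score to the planned t-test.

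What is at stake is the number of patients actually available for the primary comparison. Placebo is the smallest arm at 50, so it governs the precision of every comparison against placebo. If the 250 shrinks before the final sample, the power quoted for the trial describes more patients than will be analysed.

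**Working it through.** **Inputs from the article.** Total 250, counted at enrolment; ratio 1:2:2; difference 1.5 mg/L; standard deviation 3.5 mg/L; two-sample t-test, two-sided α = 0.05; stated power at least 80%.

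**Assumed input.** The article gives no loss rate. I take total loss *d* between enrolment and the week-4 CRP as 0% to 30%, equal across arms and unrelated to outcome.

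**Step 1: the arms as printed.** 100 + 100 + 50 = 250, and 50:100:100 = 1:2:2. The sum and the ratio are right. They need 250 of 250 enrolled, which is zero loss.

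**Step 2: power as printed, with no loss.** SE = SD × √(1/n₀ + 1/n₁); noncentrality = difference / SE; degrees of freedom = n₀ + n₁ − 2; power from the noncentral t distribution.

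- Fluticasone versus placebo: SE = 3.5 × √(1/50 + 1/100) = 0.606; noncentrality = 1.5 / 0.606 = 2.474; 148 degrees of freedom; power **69.1%**.
- Both active arms pooled versus placebo, 200 versus 50: SE = 0.553; noncentrality 2.711; power 77.0%.
- A 100 versus 100 comparison: SE = 0.495; noncentrality 3.030; power 85.4%.

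The stated minimum of 80% is reproduced only for 100 versus 100, which is not a placebo comparison. It is missed for fluticasone versus placebo before any patient is lost.

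**Step 3: power with assumed loss.** Remaining total = 250 × (1 − *d*), split 1:2:2.

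| Assumed total loss | Placebo / fluticasone / combination | SE (fluticasone v placebo) | Power, fluticasone v placebo | Power, pooled active v placebo |
|---|---|---|---|---|
| 0% | 50 / 100 / 100 | 0.606 | 69.1% | 77.0% |
| 10% | 45 / 90 / 90 | 0.639 | 64.4% | 72.6% |
| 20% | 40 / 80 / 80 | 0.678 | 59.3% | 67.5% |
| 30% | 35 / 70 / 70 | 0.725 | 53.6% | 61.6% |

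Each further 10% of loss costs about 5 to 6 percentage points on fluticasone versus placebo.

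**Step 4: what counting at randomisation would require.** If a fraction *p* is lost before randomisation, entry must be 250 / (1 − *p*):

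- 250 / 0.90 = 277.8, so 278 patients (28 more);
- 250 / 0.80 = 312.5, so 313 patients (63 more).

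Here *p* is pre-randomisation loss only. If part of the 10% or 20% falls after randomisation, fewer extra entrants are needed to randomise 250, but some week-4 samples are still missing. At best this returns the trial to the 69.1% of Step 2.

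**Step 5: the separate shortfall.** At a 1:2 ratio, 80% power needs 65 placebo and 130 fluticasone patients with a week-4 value (80.2%). That is 65 + 130 + 130 = 325 evaluable, and with 10% total loss 325 / 0.90 = 361.1, so 362 entering.

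**The case against.** The strongest reply is that the word for enrolment is used loosely in the sample size section. It moves at once to numbers assigned and exposed during the treatment phase, and elsewhere all participants are said to be randomised. The 250 could be the randomised target, with run-in failures replaced under a fuller protocol that is not shown. That reading is possible. It conflicts with how the article uses enrolment in its sections on exacerbations and eligibility, and it would still leave no stated allowance for missing week-4 samples. The objection therefore supports a request for clarification and does not remove the point. Nor is this only a detail left to another document, because the article itself prints the count and the arm sizes.

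A second reply is that the exacerbation rules limit loss: patients who regain stability for at least 2 weeks resume the study. This stands, and it matters most in the withdrawal phase. It does not cover withdrawn consent, death, failure to return or a missing final sample.

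Two stronger readings are tempting, and the document supports neither. A reader might infer that the 100/100/50 arms will not be reached. That needs a loss rate, and none is given. A reader might also infer from the Discussion that the authors expect drop-out in this trial. The sentence says that "follow-up longer than four weeks would be associated with increased drop-out rates". It explains why a longer design was rejected, puts no figure on loss in this one, and does not address loss before randomisation.

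It is also fair to say that the larger problem is the 69% power with no loss. Loss adds to that shortfall but does not cause it.

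**Conclusion.** The point holds as a mismatch between where the 250 is counted and what it is said to deliver. The printed arms require zero loss over 8 weeks, and complete primary data require zero loss over 12. The additional cost in power for fluticasone versus placebo is about 5 percentage points at an assumed 10% loss, 10 at 20% and 15 at 30%, on top of a starting value of 69% against the stated minimum of 80%.

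These figures rest on the article's difference and standard deviation, on loss rates that are my assumption, and on loss that is even across arms and unrelated to CRP. If 250 was meant as the number randomised, the pre-randomisation part becomes a matter of wording, and only loss before the week-4 sample remains. No sum in the article is wrong on this point; the unstated assumption of zero loss is what needs correcting.

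**What to change.** In the Sample size calculation section:

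1. State whether 250 is the number entering run-in or the number randomised, and use the same term in the abstract.
2. State two assumed losses separately: before randomisation, and between randomisation and the week-4 CRP sample.
3. Give the expected evaluable number in each arm and restate power for each planned comparison on those numbers.

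This is a change of text and costs nothing.

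Redefining 250 as the number randomised is optional. It would mean about 28 more patients entering run-in if 10% are lost before randomisation, or about 63 more if 20% are. It deals only with loss before randomisation and does not by itself bring fluticasone versus placebo to 80%. If the total is recalculated to meet the stated power, the new figure should be the number evaluable, with entry derived from it, so that the same gap does not recur.

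### The stated power of at least 80% does not follow from the plan's own inputs: 50 placebo versus 100 fluticasone patients give about 69%

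*Protocol article*

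**What the plan says.** The Sample size calculation section of the protocol article gives a complete set of inputs.

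- Total: "We will enroll 250 participants with COPD for this study".
- Arms: "100 participants to be assigned to fluticasone and combination treatment groups, respectively", with 50 on placebo.
- Effect and variability: "we anticipate that fluticasone relative to placebo will lower baseline CRP levels by ~1.5 mg/L with standard deviation of 3.5 mg/L".
- Test, significance level and power: "using independent two sample t-test at alpha of 0.05 (two-tailed) and a power of ≥80" per cent.

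The Overview of the study design section confirms the allocation as a "1 (placebo arm) to 2 (fluticasone arm) to 2 (combination arm) distribution ratio", so the placebo arm of 50 is a design choice and not a slip in one place. The Main analysis section names between-group t-tests on the four-week change in CRP as the primary analysis. A mixed model is added to adjust for baseline differences. The sample size section states no allowance for drop-out and no adjustment for more than one comparison.

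**The concern.** The smaller arm dominates the precision of a two-group comparison. With 50 on placebo, the standard error of the difference is considerably larger than with two arms of 100, and a standardised effect of 1.5/3.5 = 0.43 is too small for 50 versus 100 to detect with 80% power. The power statement therefore looked as if it had been worked out for some other comparison.

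This is the power of the primary endpoint. The article's Discussion relies on it too, when it rejects invasive airway sampling partly because slower recruitment would cost power on CRP. If the true figure is well under 80%, a non-significant result is weaker evidence against the assumed effect than the article leads its reader to think.

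**Working it through.** **Inputs, all from the protocol article**

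| Quantity | Value | Section |
|---|---|---|
| Difference, fluticasone vs placebo | 1.5 mg/L | Sample size calculation |
| Standard deviation | 3.5 mg/L, read as the common SD of the quantity compared | Sample size calculation |
| Test | independent two-sample t, two-sided 0.05 | Sample size calculation |
| Placebo / fluticasone / combination | 50 / 100 / 100 | Sample size calculation; ratio in Overview of the study design |
| Stated power | at least 80% | Sample size calculation |

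**Step 1. Try to reproduce the stated figure for the stated contrast (50 vs 100)**

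SE = SD × √(1/n₁ + 1/n₂) = 3.5 × √(1/50 + 1/100) = 0.606

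Noncentrality = 1.5 / 0.606 = 2.474, with df = 50 + 100 − 2 = 148

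Power = P(|T| > t₀.₉₇₅,₁₄₈), where T is noncentral t and t₀.₉₇₅,₁₄₈ = 1.976. This gives **0.691**.

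Normal approximation: Φ(2.474 − 1.960) = 0.697 from the unrounded noncentrality.

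The stated 80% is not reproduced. The shortfall is 80 − 69.1 = 10.9 points, and the type II error is 1 − 0.691 = 0.309.

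**Step 2. Try the other readings**

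| Reading | Power | Consistent with the text? |
|---|---|---|
| 50 vs 100, two-sided 0.05 | 69.1% | Yes, this is the stated contrast |
| 50 vs 200 (active arms pooled), two-sided 0.05 | 77.0% | Possible reading of Main analysis |
| 50 vs 100, inputs at the most favourable rounding (1.549 and 3.45) | 73.1% | Stretches both inputs |
| 50 vs 100, one-sided 0.05 | 79.3% | No, the text says two-tailed |
| 83 vs 83 (equal thirds) | 78.4% | No, allocation is 1:2:2 |
| 100 vs 100, two-sided 0.05 | 85.4% | No, placebo has 50 |

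For the pooled row: SE = 3.5 × √(1/50 + 1/200) = 0.553, noncentrality = 1.5/0.553 = 2.711, df = 248.

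The only reading in the table that reaches 80% is 100 versus 100. Those are the sizes of the two active arms, whereas the 1.5 mg/L is defined against placebo. The one-sided test comes close but contradicts the text. Either could be how the figure arose, but the document does not say.

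**Step 3. What would give 80%**

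- Arms fixed at 50 and 100, SD 3.5: a difference of about 1.71 mg/L.
- Arms fixed at 50 and 100, difference 1.5: an SD of at most about 3.07 mg/L.
- Difference 1.5 and SD 3.5, allocation 1:2: 65 placebo and 130 fluticasone (power 80.2%). At 1:2:2 this is 65 + 130 + 130 = 325 patients, 75 more than planned.
- Difference 1.5 and SD 3.5, active arms pooled at 1:4: 54 placebo and 216 active, 270 in total.

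**Step 4. Direction of what is left out**

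The 69% assumes that every randomised patient contributes. As an illustration only, an assumed 10% loss (45 vs 90) lowers it to about 64%. If two-sided 0.05 were split equally over the two active-versus-placebo tests (0.025 each), power for one of them with full arms would be about 58%.

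**The case against.** The best counter-argument is that 69% depends on how the primary contrast is read. The Main analysis section sets patients on fluticasone, alone or with salmeterol, against placebo, and the aims and primary endpoint use similar wording. Read as one pooled comparison, power is 77.0% and the shortfall is 3 points rather than 11. The effect is also given only approximately: pooling with a difference of 1.549 mg/L reaches 79.6%, and also taking the SD down to 3.45 reaches about 80.7%.

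The pooled reading is fair as a reading of the analysis section, and 77% should be reported beside 69%. It does not rescue the claim. The sample size section ties its assumed effect to "fluticasone relative to placebo will lower baseline CRP levels by ~1.5 mg/L with standard deviation of 3.5 mg/L", which is the 50 versus 100 contrast. Pooling at the printed values still falls short. Reaching 80% takes pooling plus favourable rounding of both inputs, which is too much to ask of a plain power statement.

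A second point is that the text does not say whether 3.5 mg/L is the SD of the change or of the CRP level. If it were the SD of the level, the SD of the change would depend on a within-patient correlation that the article does not give. But the SD is quoted with the effect and used in a t-test on CRP from baseline, so its plain meaning is the SD of what is compared.

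Baseline adjustment might recover some power, but the stated calculation rests on an unadjusted t-test and gives no correlation that would support a gain. Nor can a separate analysis plan help: the inputs and the claim stand together here and do not agree.

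**Conclusion.** The concern holds. With the inputs as printed, the fluticasone versus placebo comparison has 69.1% power, about 11 points below the stated minimum, and would miss the assumed effect in about 31% of trials. If the active arms are pooled, power is 77.0% and the miss rate 23%. No two-sided placebo comparison at the printed values and planned arm sizes reaches 80%.

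This rests on 3.5 mg/L being the common SD of the compared quantity, on no losses, and on no adjustment of alpha. Losses or an alpha adjustment would lower the figure further. Because a stated design property of the primary endpoint is wrong as written, it must be corrected. The design need not change for the statement to become true.

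**What to change.** Replace the power statement in the Sample size calculation section with one that the inputs support, for example: with 50 placebo and 100 fluticasone patients, a two-sided 0.05 t-test has 69% power for a difference of 1.5 mg/L (SD 3.5 mg/L), or 80% power for about 1.71 mg/L. Say that 3.5 mg/L is the SD of the change in CRP, if that is what is meant. If the primary contrast is meant to pool the active arms, say so and give 77%.

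If the higher figure comes from a different analysis, such as one adjusted for baseline, derive the power for that analysis and state every input, including the assumed correlation.

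The cost is one corrected sentence and a less favourable number; no patients are added. Keeping 80% power for 1.5 mg/L by enlarging the trial at 1:2:2 would instead take 325 patients, 75 more than planned.

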#### Ethical considerations

The protocol and procedures as described above have received institutional approval from the University of British Columbia/Providence Research Ethics Board, as well as from all local institutional ethics review board of each participating site. The funding for the study is from GlaxoSmithKline (Mississauga, ON). The funding source has no role in the design, conduct, analysis, interpretation, or reporting of the study and will not have access to the raw data. All data will be housed at the James Hogg iCAPTURE Center in Vancouver, BC.

## Discussion

In this paper, we have reported the background, the rationale, and the study protocol for a unique multi-center randomized controlled trial whose main outcome is a biochemical measurement (i.e. CRP). The study will test the hypothesis that inhaled corticosteroids alone or in combination with a long-acting β_2_-adrenoceptor agonist will reduce CRP levels in stable COPD patients. To our knowledge, this is the first clinical trial in COPD whose main outcome is serum CRP. Additionally, this study will be able to determine the effects of these medications on other relevant inflammatory biomarkers and likely provide a solid biological rationale for the clinical effects of inhaled corticosteroids and combination therapy in COPD.

There are certain limitations of this trial. Firstly, the study will not measure any parameters of inflammation in the lung. We decided against collecting biological samples from the airways because: 1) a recently conducted and published randomized controlled trial demonstrated that combination therapy reduces airway inflammation [20,21]; 2) there remains considerable amount of controversy regarding the utility of exhaled condensates and induced sputum in assessing airway inflammation in COPD [28]; 3) more invasive measurements (e.g. bronchoscopy) would have significantly reduced the projected recruitment rate of participants, reducing the power of the study to detect relevant differences in CRP; and 4) the primary focus of this study was to assess the effects of combination and steroid therapy on systemic inflammation. Secondly, the study has a relatively short follow-up period. We decided against a longer period of follow-up for pragmatic reasons. In our previous pilot study, we observed significant changes in CRP with inhaled corticosteroids after only 2 weeks of treatment [15]. Additionally, we were concerned that follow-up longer than four weeks would be associated with increased drop-out rates, and exacerbations, reduced compliance with the study medications, and changes in medications (both pulmonary and nonpulmonary drugs) that may alter CRP levels. Thirdly, we cannot be certain that changes in CRP levels will necessarily result in significant changes in health outcomes of COPD patients, though there is a body of indirect evidence suggesting that they do [6,14,17]. Additional work is needed in future studies to establish a causal link between CRP and health outcomes in COPD.

In summary, the present study will determine whether inhaled fluticasone alone or in combination with salmeterol has any significant systemic anti-inflammatory effects. Since systemic inflammation has been linked with a variety of important complications in COPD including peripheral muscle dysfunction, cachexia, cardiovascular complications and cancer, if these medications do indeed reduce systemic inflammation, this will provide an important biological mechanism by which they improve health outcomes in COPD. Additionally, this study will serve as an important template for future studies, linking systemic inflammation with clinical outcomes in COPD.

